#### Possible Identifying Characteristics for the Presence of PsA in Psoriasis

The identifying value of various clinical markers for the presence of PsA in psoriasis will be processed as independent variables in a univariate logistic regression model. Diagnosis of PsA (yes/no) will be the dependent variable. Variables that are statistically related to the outcome (*P*≤.20 in univariate modeling) and are clinically and methodologically feasible (based on a favorable balance between prevalence in the cohort, effect size, and ease of measurement) will be selected. The subsequent selection of variables will be tested in a multivariable logistic regression model with backward stepwise selection. Sensitivity analysis will be performed by reclassifying patients with an uncertain diagnosis as cases. The number of possible independent variables will be limited based on a minimum of 10 events (PsA diagnoses) per variable. Bootstrapping will be used to assess the internal validity of the model in terms of overoptimism and shrinkage.

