To ensure early adequate treatment and prevent (irreversible) morbidity, early recognition and early referral to a rheumatologist are key. The combined guidelines of the American Association of Dermatologist and the National Psoriasis Foundation calls screening of patients with psoriasis for PsA “essential at each visit” [12]. However, recognition of inflammatory joint complaints is not part of the dermatological scope. In addition, due to a large prevalence of noninflammatory joint complaints, referral of all patients with musculoskeletal pain is considered an unnecessary drain of resources. Therefore, about one in three patients with PsA remain unrecognized in the dermatological clinic [1] and are at risk for irreversible damage.

To aid the recognition of PsA by dermatologists, several screening questionnaires have been developed [13-16]. Most of these are based on multiple patient-reported signs or symptoms and result in a cumulative score. Referral to a rheumatologist is recommended when a certain score is reached. Unfortunately, testing of these questionnaires in new cohorts often had disappointing results [17,18]. The long average lag time between psoriasis and PsA also necessitates repeated use of a screening tool on a regular basis. However, none of the questionnaires were validated for reuse. These are all clues that current referral strategies are inadequate.

By screening a psoriasis population for the presence of concomitant PsA, we want to determine the prevalence of (undiscovered) PsA in this group. During this screening visit, we will gather data about several clinical characteristics. These will be used to ultimately develop a new or enhance an existing instrument for rheumatologic referral. This study is therefore called the Discovery of Arthritis in Psoriasis Patients for Early Rheumatology Referral (DAPPER).

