### Design

The DAPPER study is a monocenter observational study with a follow-up of 1 year. We will examine 300 patients stratified 1:1:1 according to current dermatological treatment (topical or UV therapy only, conventional systemic medication but no biologicals, biological therapy).

The initial screening at the dermatology department will include a 68 tender joint count, 66 swollen joint count, a dactylitis count (0-20), and enthesitis scores (Leeds Enthesitis Index [LEI] [19] and the enthesitis score of the Spondyloarthritis Research Consortium of Canada [SPARCC] [20]). Inflammatory back pain will be assessed via the criteria of the Assessment of Spondyloarthritis International Society [21]. At this study visit, no laboratory tests or imaging will be performed for diagnostic purposes.

To investigate possible identifying characteristics or confounders for the detection of PsA, the study visit will also be used to gather demographical data (comorbidity, treatment data, and clinical characteristics of the skin). An example of the interview guide used is shown in Multimedia Appendix 1.

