### Participants

All patients with a clinical diagnosis of psoriasis who are treated at the outpatient clinic are eligible for this study. Neither current nor previous treatment by a rheumatologist nor a previous diagnosis of PsA are exclusion criteria. Patients must be 18 years or older and be able to give written informed consent.

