#### Study Size

For the logistic model, we aim to use 5 to 10 independent variables. The number of independent variables used in the model will be restricted to 1 per 10 events (ie, 1 per 10 PsA cases). Therefore, we aim to have 50 to 100 PsA cases. Assuming a prevalence of PsA of 20% to 30% [1], this means we need 167 (prevalence 30%, 5 predictors) to 500 (prevalence 20%, 10 predictors) patients with psoriasis. Using a total number of 300 patients, we expect to find up to 60 to 90 PsA cases, ensuring we can incorporate 6 to 9 independent variables.

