### Outcome Variables

#### Prevalence of PsA

To ascertain the presence of PsA, we will ask the patient about joint and enthesis complaints (location, pattern, and intensity), morning stiffness (duration), and whether or not they ever had a diagnosis of arthritis. For confirmation of arthritis, dactylitis, or enthesitis, we will perform joint counts (swollen, tender, and dactylitis) and enthesitis indices (LEI and SPARCC). After referral, the diagnosis of PsA or alternative diagnosis will be retrieved from (the correspondence gathered in) the electronic patient file.

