#### Possible Identifying Characteristics for the Presence of PsA in Psoriasis

We will gather information about demographic variables, comorbidity, intoxications, and family history. Family history and comorbidity will be targeted at diseases that are associated with spondyloarthritis, such as uveitis, psoriasis, and inflammatory bowel disease. Next to that, the Charlson Comorbidity Index [26] and Functional Comorbidity Index [27] will be used to evaluate a total comorbidity burden. Data about comorbidity specifically associated with either psoriasis or PsA (eg, hepatic [28], psychological [29], and cardiovascular [30] diseases) will be added. In addition, current and previous treatment for either PsA or psoriasis will be noted. Severity and location of psoriasis (via Psoriasis Area and Severity Index [31] and body surface amount will be noted. Nail involvement will be assessed via Nail Psoriasis Severity Index [32] and Nijmegen Nail Psoriasis Activity Index Tool [33]. Three of the currently used screening questionnaires (ie, Psoriasis Epidemiology Screening Tool [PEST], Toronto Psoriatic Arthritis Screen [ToPAS], and Psoriatic Arthritis Screening and Evaluation [PASE]) will be used to collect clinical characteristics that have been previously discovered in their development [13-15].

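### The referral model counts previously known PsA as events, so the stated 60–90 events and 6–9 variables overstate what the study supports for undiscovered PsA (about 20–30 events and 2–3 variables on the protocol's own one-in-three figure)

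*Protocol article*

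**What the plan says.** All places are in the protocol article.

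- **Outcome of the model** (Statistics, Possible Identifying Characteristics): "Diagnosis of PsA (yes/no) will be the dependent variable". There is no restriction or split by known versus new disease. The only sensitivity analysis named for the model reclassifies uncertain diagnoses as cases.
- **Who enters the cohort** (Participants): "Neither current nor previous treatment by a rheumatologist nor a previous diagnosis of PsA are exclusion criteria".
- **Event count** (Study Size): an overall PsA prevalence of 20% to 30% in 300 patients gives 60 to 90 cases, "ensuring we can incorporate 6 to 9 independent variables" at one variable per 10 PsA cases. The stated aim is 5 to 10 variables.
- **Purpose of the tool** (Introduction): an instrument for rheumatologic referral, motivated by the statement that "about one in three patients with PsA remain unrecognized in the dermatological clinic". Under Referral and Referral Criteria, a patient is referred only when not under current rheumatological care.
- **Known versus new** (Aim): the primary objective names very early, newly discovered and known PsA as separate categories.
- **Candidate data** (Outcome Variables, Possible Identifying Characteristics): "current and previous treatment for either PsA or psoriasis will be noted".
- **Precision claim** (Discussion): the expected 60 to 90 cases are set against earlier tools developed on 17 and 12 PsA cases, and a third with 30 cases among its dermatology recruits.

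**The concern.** A referral tool is used on patients whose PsA has not yet been picked up. The model is fitted to a mixture in which, on the Introduction's figure, most events would be patients whose PsA is already recognized. Coefficients, AUC, sensitivity and specificity from that mixture describe all PsA. They need not carry over to the undiagnosed subset, and no planned analysis would show whether they do. Bootstrapping addresses overfitting within the sampled mix. It does not change which patients make up the mix.

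Two consequences follow. First, the stated model capacity is computed from all PsA and is not available for the undiscovered-PsA question. Second, PsA treatment is collected under the heading of identifying characteristics, and nothing in the selection rule excludes it. The rule is P≤.20 in univariate modelling plus feasibility, judged by prevalence, effect size and ease of measurement. In known cases PsA treatment follows from the diagnosis, so it could pass that screen easily without helping to find undiagnosed disease.

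**Working it through.** **Inputs.** N = 300 (Design: "We will examine 300 patients stratified 1:1:1 according to current dermatological treatment"). PsA prevalence 20–30% and 10 events per variable (Study Size). Unrecognized share of PsA about 1/3 (Introduction). That this share applies to this academic, treatment-stratified cohort is an assumption.

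**Step 1: reproduce the article's figures.**
- Events = N × prevalence: 300 × 0.20 = 60 and 300 × 0.30 = 90.
- Variables = events / 10: 6 and 9.
- Required N = 10 × variables / prevalence: 50 / 0.30 = 167 and 100 / 0.20 = 500.

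All agree with Study Size. The arithmetic is right; the issue is which cases are counted.

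**Step 2: count newly discovered PsA only.** Events = N × prevalence × unrecognized share; variables are rounded down.

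| Unrecognized share | Events (20% to 30% prevalence) | Variables at 10 events each |
|---|---|---|
| 25% (assumed) | 15 to 22.5 | 1 to 2 |
| 1/3 (Introduction) | 20 to 30 | 2 to 3 |
| 40% (assumed) | 24 to 36 | 2 to 3 |
| 50% (assumed) | 30 to 45 | 3 to 4 |

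At one third, the known cases number 60 − 20 = 40 to 90 − 30 = 60. That leaves 260 to 240 participants without known PsA, of whom 20/260 = 7.7% to 30/240 = 12.5% would be newly found.

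**Step 3: compare with the article's own rule.**
- Keeping 6 or 9 variables gives 20/6 = 30/9 = 3.3 newly discovered events per variable, against the stated minimum of 10.
- The planned minimum of 5 variables needs 50 such events. In 300 patients that requires an unrecognized share of 50/90 = 56% (prevalence 30%) or 50/60 = 83% (prevalence 20%).
- At a one-third share, 50 events would need 50 / (0.30 × 1/3) = 500 to 50 / (0.20 × 1/3) = 750 patients.

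**Step 4: precision in the subset.** For illustration, an observed sensitivity of 80% (a hypothetical value) has a Wilson 95% interval of 58–92% with 20 cases and 63–90% with 30.

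**Step 5: the comparison in the Discussion.** 20–30 newly discovered cases still exceed 17 and 12, but do not exceed the 30 dermatology-recruited cases of the third tool.

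**The case against.** The strongest reply is that the outcome matches the written secondary objectives. These ask for parameters associated with the presence of PsA and for a screening tool for concomitant PsA. An all-PsA model is a legitimate answer to the first of these, and a reader who infers a contradiction between objective and model goes too far. The mismatch is with the referral purpose, and that part stands.

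Several stronger readings are tempting but not supported:

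- **The known two thirds are all treated.** The Introduction says only that about one third go unrecognized. It does not say that the rest are treated or under rheumatological care. Known PsA outside such care remains referable, so 20–30 may be somewhat low as a count of referable cases.
- **A previous arthritis diagnosis is a predictor.** The question "whether or not they ever had a diagnosis of arthritis" stands under Prevalence of PsA and serves to ascertain the outcome. It is not listed as a candidate.
- **Questionnaire items carry the earlier diagnosis into the model.** No item of the three questionnaires is shown, so this cannot be judged.
- **PsA treatment will be a predictor.** The article says only that treatment will be noted, and Design speaks of identifying characteristics or confounders. The plan permits this use; it does not announce it.
- **The precision claim fails altogether.** It weakens mainly against the third tool. The article does not say whether the 17 and 12 cases were known or new.

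The size of any distortion in the coefficients cannot be estimated from the document. Restricting the cohort would also not remove masking of joint signs by treatment, since two of the three strata receive systemic or biological therapy for the skin. Finally, a restricted model with 2–3 variables is less stable and falls below the planned minimum of 5. That is a reason not to make it the sole or main model.

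**Conclusion.** The point holds in a limited form and should be fixed. Participants, Study Size and the model specification, read together, make known PsA count as events in a model meant to yield a referral tool, and no planned analysis isolates the patients for whom referral is in question. No single sentence says that known cases enter the model; it follows from those three sections.

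For undiscovered PsA the study can expect about 20–30 events and 2–3 variables rather than 60–90 and 6–9, provided the one-in-three share holds here. Across a share of 25–50% the range is 15–45 events and 1–4 variables, always below the planned minimum of 5.

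The consequence is bounded. The model serves secondary objectives, the primary prevalence estimate is unaffected, and the Discussion already requires external validation before the tool is used.

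**What to change.** 1. Prespecify that the model's AUC, calibration, sensitivity and specificity are also reported in participants without a previous PsA diagnosis and not under rheumatological care, with newly confirmed PsA as the outcome. Add a refit restricted to that subset, with few prespecified or penalised predictors, as a prespecified analysis. The all-PsA model can stay.
2. State that current or previous PsA treatment is not a candidate predictor, because it follows from the diagnosis. It can still be recorded and described.
3. Reword Study Size so that 60–90 events and 6–9 variables refer to all PsA. Give about 20–30 events and 2–3 variables for undiscovered PsA, with the one-third share named as an assumption. Qualify the Discussion's precision claim accordingly, mainly against the 30 dermatology-recruited cases.

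Cost: wording in the analysis plan, a less favourable stated capacity, and wide intervals in the subset. No new data are needed, because the primary objective already requires known versus new status and the referral rule already requires current rheumatological care to be established.

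### The 10-events-per-variable limit counts only variables in the model, although a much longer list is first screened on the outcome, so it does not control overfitting

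*Protocol article*

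**What the plan says.** Protocol article, Study Size: "For the logistic model, we aim to use 5 to 10 independent variables", and "The number of independent variables used in the model will be restricted to 1 per 10 events". With 300 patients and an assumed PsA prevalence of 20% to 30%, it expects 60 to 90 cases and so 6 to 9 variables.

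Outcome Variables, on possible identifying characteristics, lists what will be collected: demographics, intoxications, family history, comorbidities with two comorbidity indices, treatments, skin severity and location, and two nail scores. It adds "Three of the currently used screening questionnaires" as the source of further characteristics.

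Statistics, under the same heading, first tests the markers one at a time against PsA diagnosis. Markers with P≤.20 go forward if they are also judged feasible, "based on a favorable balance between prevalence in the cohort, effect size, and ease of measurement". Backward stepwise selection follows. The section then says "The number of possible independent variables will be limited based on a minimum of 10 events (PsA diagnoses) per variable" and "Bootstrapping will be used to assess the internal validity of the model in terms of overoptimism and shrinkage".

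The article does not give the number of candidates, the removal threshold or the point at which the limit applies. It also does not say whether selection is repeated in each bootstrap sample.

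**The concern.** A limit on variables per event guards against overfitting only if it counts every parameter that had a chance to enter the model. Here the outcome helps to choose variables three times: through the univariable P value, through the observed effect size, and through backward elimination. Study Size counts only what enters the model.

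The stake is the referral tool. Selection from a long list lets noise predictors in and makes predicted risks too extreme in new patients. If internal validation does not account for that selection, the reported performance will be too favourable. This matters because the Introduction justifies the study partly by the disappointing results of earlier questionnaires in new cohorts, and the Discussion expects a more precise model on the strength of 60 to 90 cases.

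**Working it through.** **Step 1. The plan's own figures reproduce.** N = 10 × predictors / prevalence: 50/0.30 = 167 and 100/0.20 = 500. Cases at N = 300: 300 × 0.20 = 60 and 300 × 0.30 = 90. Variables = cases/10 = 6 to 9.

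**Step 2. Count the candidates.** The article gives no number, so this is a count from Outcome Variables:
- demographics as a single entry (1) and intoxications (1)
- family history of three named diseases (3)
- uveitis and inflammatory bowel disease as comorbidities (2)
- two comorbidity indices (2)
- hepatic, psychological and cardiovascular disease (3)
- current and previous treatment (2)
- psoriasis severity index, location and body surface (3)
- two nail scores (2)

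That makes 19, or 22 with each of the three questionnaires counted once. Splitting demographics or using single questionnaire items raises the number. 40 and 60 are used below as assumed values.

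**Step 3. Events per candidate = cases / candidates.**
- 22 candidates: 60/22 = 2.7 to 90/22 = 4.1
- 40 candidates: 1.5 to 2.3
- 60 candidates: 1.0 to 1.5

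Ten events per candidate at 22 candidates would need 220 cases: 220/0.30 = 734 to 220/0.20 = 1,100 patients.

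**Step 4. What the P≤.20 screen lets through.** If all candidates were independent noise, 0.20 × 20 = 4, 0.20 × 40 = 8 or 0.20 × 60 = 12 would pass. The binomial probability that more than 6 of 40 pass is 0.71, and that more than 9 of 60 pass is 0.79. The screen alone could therefore fill the allowance with noise.

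**Step 5. Simulated effect on the bootstrap.** Taken from the plan: n = 300, prevalence 20% and 30%, P≤.20 screen, cap at events/10. Assumed: 5 true predictors with log-odds ratio 0.5 per SD, correlation 0.1, cap filled by smallest P, removal at 0.05 or 0.10. There were 120 data sets with 60 bootstraps each. Ranges run over prevalence and removal threshold.

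| Candidates | True AUC optimism | Share found, final model refitted only | Share found, screen, cap and backward steps repeated |
|---|---|---|---|
| 10 | 0.026-0.036 | 40-57% | 79-96% |
| 20 | 0.028-0.034 | 43-51% | 112-119% |
| 40 | 0.037-0.047 | 32-40% | 103-115% |
| 60 | 0.043-0.057 | 27-34% | 95-114% |

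A bootstrap of the final model alone therefore misses 49-57% at 20 candidates, 60-68% at 40 and 66-73% at 60. It reports an optimism of only 0.014-0.016 throughout. Subtracting that from the true optimism in each setting, the corrected AUC would still be too high by 0.014-0.019 at 20 candidates, 0.023-0.031 at 40 and 0.029-0.041 at 60. At 40 candidates the true calibration slope is 0.80-0.83. The final-model bootstrap gives 0.92-0.93, and repeating the selection gives 0.79-0.80.

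**Step 6. Sensitivity to the assumptions.** With 3 weaker predictors (log-odds ratio 0.35, correlation 0.2), 25% prevalence, a cap of 7 and 40 candidates, apparent AUC is 0.701 and true AUC 0.652. Refitting only the final model reports 0.690, so it finds (0.701 − 0.690)/(0.701 − 0.652) = 0.011/0.049 = 22% of the optimism. Repeating the selection reports 0.642, a slight over-correction.

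**The case against.** A reader might infer that the bootstrap is bound to miss most of the optimism, because the judgement on effect size cannot be replayed and so only the finished model can be resampled. The documents do not support this. The Statistics section neither states nor excludes that selection is repeated, and a condensed article may leave that to an analysis plan that is not shown. Nor does the inference follow: the P≤.20 screen, the cap and backward elimination can all be repeated even if the judgement cannot. Neither simulation models the judgement step, so neither measures the harm it does.

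The position of the cap is also inferred. The Statistics wording speaks of possible variables and could mean a cap on candidates. Study Size points the other way, and a list already held to 6 to 9 would hardly need a P≤.20 screen. The documents describe no separate reduction blind to the outcome.

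The sizes rest on assumed candidate numbers and effect sizes, and no Monte Carlo error is available for 120 data sets. Pure noise is a poor model for candidates partly drawn from earlier questionnaires, so Step 4 is an extreme case.

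Finally, the tool is a secondary objective, and the Discussion requires a second cohort before it is implemented. All these points limit the size and certainty of the harm. They do not change the fact that the limit, as Study Size words it, leaves screened candidates uncounted, or that effect size is a stated criterion for choosing among them.

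**Conclusion.** The concern holds for the limit and for the effect-size criterion. On the more natural reading, ten events per variable describes the model that is entered, not the search that leads to it. The search has about 2.7 to 4.1 events per candidate at 22 candidates, and fewer if questionnaire items are tested singly. The limit therefore does not control overfitting, and a judgement made on observed effect size cannot be reproduced exactly in a resample.

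The bootstrap part is conditional. Only if the final model alone is refitted does it miss about half of the AUC optimism at 20 candidates and about 60-73% at 40 to 60, under the main simulated assumptions. In absolute terms that is an AUC too high by roughly 0.01 to 0.04. Repeating the screen, cap and backward steps recovers nearly all of the optimism, and slightly over-corrects in several settings.

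Severity is moderate: the prevalence estimate is untouched, and external validation stands between this model and its use.

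**What to change.** 1. In Statistics, delete effect size from the feasibility step. Prune candidates on prevalence in the cohort and ease of measurement only, by someone blind to PsA status.
2. In Study Size and Statistics, count all candidate parameters tested against PsA towards the 10-events limit, not only those in the final model. Otherwise, stop presenting the limit as protection against overfitting.
3. State that any remaining data-driven selection (P≤.20 screen, cap, backward steps) is repeated in every bootstrap sample, and shrink the final coefficients by the resulting slope.

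Item 3 matters even after pruning: with only 10 candidates in the simulation, refitting the final model alone still found just 40-57% of the optimism. Penalised regression on the pre-set list is an option, not a requirement.

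The cost is a change of wording, some programming, fewer candidates (and so the risk of dropping a useful one) and a slightly lower reported AUC. No further data are needed.
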